## **10. SAFETY EVALUATION**

### **10.1 Adverse events**

Events that occur between the observation start date and the observation end date (during the observation period) will be included in the analysis. Adverse event summaries according to system organ class and type of event will be prepared using MedDRA/J.

- 1) The number of patients with adverse events and their incidence (100 x no. of patients with adverse events / no. of ITT patients) will be determined according to treatment group. The incidence of adverse events will be compared between groups using the chi-square test.
- 2) Incidence will be determined according to system organ class and event type (preferred term) based on terminology conversions using MedDRA/J, and the chi-square test will be used to compare these incidences across groups.
- 3) A frequency distribution for each level of severity will be determined based on the converted terms. If the same type of event occurs more than once in the same subject, the severest of these events will be used.

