### **5.3. Criteria for subject discontinuation or completion**

If it is determined that continued observation of a subject is impossible due to the following reasons, that subject will be withdrawn from the study and the reason and date for this recorded. All necessary observations and tests will be performed at this time, and efficacy and safety evaluations performed.

- 1) Subject requests discontinuation or withdraws consent
- 2) A serious adverse event occurs which makes continuation problematic
- 3) Any event described in 6.3.3. occurs

- 4) Drug withdrawal lasts longer than 4 weeks
- 5) Any other reasons which lead the investigator/subinvestigator to consider continued participation problematic

Observation will also be discontinued for patients who discontinued taking study drugs.

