## 6.9 Handling of patients with study drug administration errors

For all of the analyses, the data for these patients will be analyzed as data for the groups allocated to a treatment.

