### **10.5 Hemorrhagic adverse events**

Hemorrhagic adverse events will be analyzed in the same manner as indicated in subsections 1) and 2) of section 10.1 (adverse events). Incidence will be determined for all hemorrhagic events and for hemorrhage determined to be severe or life-threatening based on the GUSTO bleeding criteria. Incidence will be determined according to system organ class and event type (preferred term) based on terminology conversions using MedDRA/J, and the chi-square test will be used to compare these incidences across groups.

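### Severe bleeding, all bleeding and SAEs are compared as crude percentages of ITT patients by chi-square; if drug stopping differs by arm, the arm that stops more shows a falsely low percentage

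*Supplement*

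**What the plan says.** SAP 10.1 fixes the measure and the test. It states that "incidence (100 x no. of patients with adverse events / no. of ITT patients) will be determined according to treatment group", and that "The incidence of adverse events will be compared between groups using the chi-square test". It also limits the numerator: "Events that occur between the observation start date and the observation end date (during the observation period) will be included in the analysis".

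SAP 10.3 carries this to serious adverse events. SAP 10.5 carries it to bleeding: "Hemorrhagic adverse events will be analyzed in the same manner as indicated in subsections 1) and 2) of section 10.1", and "Incidence will be determined for all hemorrhagic events and for hemorrhage determined to be severe or life-threatening based on the GUSTO bleeding criteria". Severe or life-threatening bleeding by GUSTO is the one specific clinical event named as a safety endpoint (SAP 2.3, protocol section 9).

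The observation period is not the same for everyone. Protocol 11.4.1 plans 1 to 3.5 years. The v1.3 dates in protocol 10.2 (enrolment October 2013 to March 2017, study to March 2018) extend this to about 4.5 years. Protocol 5.3 adds: "Observation will also be discontinued for patients who discontinued taking study drugs". SAP 7 also ends observation at any evaluated event or after more than four weeks off drug.

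Elsewhere the SAP does use time. Person-years by group are derived (6.2.4, 8.2.2), and 9.1 analyses the primary endpoint by log-rank, Kaplan-Meier, Cox and person-year incidence. SAP 9.2.2 applies log-rank, Kaplan-Meier and Cox to ICH or SAH. Section 10 uses none of these methods.

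**The concern.** A patient who stops drug after three months can contribute a bleed for three months only, yet counts as a whole patient in the denominator. For a rare event the crude risk in an arm is about hazard times mean observation time. The ratio of percentages is therefore about the hazard ratio times the ratio of mean observation times. If DAPT is stopped more often, that factor is below 1 and works in favour of DAPT.

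Bleeding decides whether long-term dual therapy is acceptable. Protocol 2.1 gives serious bleeding as the reason why another long-term dual regimen is not recommended. As planned, benefit would be judged per unit of time, and most of the harm without regard to time.

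**Working it through.** **1. The plan's own figure.** This checks the accrual model used below. Inputs (SAP section 4, protocol 11.1): 4% against 2.8% a year, 2.5 years' accrual, 3.5 years in total, two-sided 0.05, 80% power.

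- Events (Schoenfeld): 4 × (1.960 + 0.842)² / (ln 0.7)² = 247.
- Event probability with uniform accrual over R and total time F: 1 − (e^(−λ(F−R)) − e^(−λF)) / (λR). This is 0.0857 at λ = 0.04 and 0.0609 at λ = 0.028, with mean 0.0733.
- N per group: 247 / 0.0733 / 2 ≈ 1,685, against the stated 1,688. The model reproduces the plan.

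**2. Model for the safety comparison.** Constant hazards; observation ends at drug stop, at recurrence or at study close.

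- From the documents: R = 2.5 and F = 3.5, or about 3.5 and 4.5 on the v1.3 dates; recurrence 0.04 (SAPT) and 0.028 (DAPT) a year; 2,000 per group; pooled dropout 5% a year.
- Assumed, because the documents give no such figures: bleeding b = 0.01 per person-year in both arms; drug stop s of 5% a year in SAPT and 5 to 30% in DAPT.

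With h = b + s + recurrence, crude risk = (b/h) × [1 − (e^(−h(F−R)) − e^(−hF)) / (hR)].

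SAPT: h = 0.01 + 0.05 + 0.04 = 0.10. Risk = 0.1 × [1 − (0.9048 − 0.7047)/0.25] = 1.99%.

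DAPT at s = 20%: h = 0.01 + 0.20 + 0.028 = 0.238. Risk = 0.0420 × [1 − (0.7882 − 0.4347)/0.595] = 1.71%. Mean observation is 1.71 years against 1.99.

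**3. Results at equal true hazards** (SAPT stop 5% a year)

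| DAPT stop per year | Crude % DAPT v SAPT | Crude ratio, 2.5/3.5 y | Crude ratio, v1.3 dates | Person-year rate ratio |
|---|---|---|---|---|
| 5% | 2.02 v 1.99 | 1.01 | 1.02 | 1.00 |
| 10% | 1.91 v 1.99 | 0.96 | 0.95 | 1.00 |
| 15% | 1.80 v 1.99 | 0.90 | 0.88 | 1.00 |
| 20% | 1.71 v 1.99 | 0.86 | 0.83 | 1.00 |
| 30% | 1.53 v 1.99 | 0.77 | 0.73 | 1.00 |

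The ratios hardly move when b is varied from 0.005 to 0.02. If the extra DAPT stops come early (10% or 20% of patients at one month, 5% a year for the rest), the crude ratio is 0.92 or 0.82.

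**4. Consequences (2.5/3.5 years)**

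- The true hazard ratio that would show as equal percentages is about the inverse of the crude ratio: 1.17 at 20% a year and 1.30 at 30%.
- The chance that chi-square declares DAPT safer when the hazards are equal (nominal 2.5%) is 6.5%, 10% and 20% at DAPT stop rates of 15, 20 and 30% a year. At 20% a year it is 6.9% for b = 0.005 and 15.7% for b = 0.02.
- Power against a true hazard ratio of 1.5 at a 20% DAPT stop rate: the crude ratio is 1.28 and the chi-square test has about 21%. Log-rank with 39.9 + 50.9 = 90.8 expected events has Φ(ln 1.5 × √(90.8/4) − 1.96) = about 49%.

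**The case against.** Much of the case for the plan stands.

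- **Part of the endpoint is covered.** A reader of section 10 alone might infer that severe bleeding gets nothing but chi-square. Intracranial bleeding is the first element of the GUSTO definition, and ICH or SAH has log-rank, Kaplan-Meier and Cox under 9.2.2. What has no time-based analysis is the GUSTO composite, extracranial severe bleeding, other intracranial bleeds, all bleeding and SAEs.
- **The bias is conditional.** A reader might infer that DAPT will look safer than it is. The documents give one dropout rate, 5% a year, with no split by arm, and at equal rates the bias is negligible. The spread of calendar follow-up is not itself a source of bias, because randomisation blocked within centre balances it. The assumed DAPT stop rates are two to six times the planned dropout. Unequal stopping is plausible, since DAPT adds a drug and protocol 5.2 foresees headache on cilostazol, but the documents do not quantify it.
- **Two things reduce the bias.** A bleed that itself causes the stop is still counted. Fewer recurrences on DAPT would lengthen its observation slightly; the model includes this, and it is why equal stop rates give 1.01 to 1.02.
- **An imbalance would be visible.** SAP 8.2.2 compares observation time between arms. It does not adjust the safety comparison, however.
- **Crude percentages by preferred term** are ordinary descriptive reporting and can stay.

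**Conclusion.** The point holds as a conditional one. If drug stopping differs by arm, the planned percentages understate risk in the arm that stops more. With the assumed rates the understatement is 4 to 23% for DAPT stop rates of 10 to 30% a year (5 to 27% on the v1.3 dates); with equal stopping it is nil for practical purposes. The arm-specific stop and bleeding rates are assumptions, and so are constant hazards.

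It is tempting to ask also for a treatment-policy analysis, an analysis of patients with at least one dose, or an on-drug analysis with a four-week tail. The documents do not support these. Observation ends at drug stop, so a treatment-policy comparison has no data to rest on. Protocol section 25 provides a visit within four weeks only for unrecovered events, and the new events it follows there are SAEs whose link to study drug cannot be denied, so it is not a general capture window. SAPT patients already take aspirin or clopidogrel at consent, so a one-dose rule would hardly separate anyone in that arm.

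Severity: should-fix.

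**What to change.** In SAP 10.3 and 10.5, for GUSTO severe or life-threatening bleeding, all haemorrhagic events and SAEs:

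- Make the between-arm comparison by time to first event within the observation period, with the methods of 9.1: incidence per 100 person-years with 95% CI, Kaplan-Meier curves, the log-rank test, and the Cox hazard ratio with 95% CI.
- Keep the crude percentages of ITT patients as description.
- Refer to 9.2.2 for ICH or SAH, so that the two analyses are read together.
- State that the comparison corrects for unequal observation time but not for informative censoring at drug stop, which the data collected under protocol 5.3 cannot resolve.

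The cost is SAP text and a few tables. Event dates (protocol 24.2), discontinuation dates (protocol 6.3.2) and person-years by group (SAP 6.2.4, 8.2.2) are already planned, and no protocol change is needed.

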### **10.2 Adverse drug reactions**

Adverse events for which a causal relationship to the study drug cannot be ruled out will be considered adverse drug reactions and analyzed in the same manner as indicated in subsections 1), 2), and 3) of section 10.1 (adverse events).

### **10.3 Serious adverse events**

Adverse events rated as "serious" in the assessment of seriousness will be considered serious adverse events and analyzed in the same manner as indicated in subsections 1) and 2) of section 10.1 (adverse events).

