### 6.3.2. All observations after first month

The following items will be observed or evaluated according to the observation schedule:

- Observation status: Ongoing or unavailable
- Date of observation (date of last information if unavailable for observation)
- Presence or absence of events
  - If events have occurred, refer to 6.3.3. *Events*.
- Presence or absence of adverse events or serious adverse events
  - If events have occurred, refer to 23. *Procedures for Adverse Events* and 24. *Evaluation of Adverse Events*.
- Modified Rankin Scale (mRS)
- Status of study drug administration
  - Administration rate:  $\geq 70\%$  or  $< 70\%$
  - Withdrawal ( $< 4$  weeks of continuous drug withdrawal): No or Yes (length)

Discontinuation ( $\geq 4$  weeks of continuous discontinuation): No or Yes (date and reasons)

- Drugs used other than study drugs
- Blood pressure

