### 6.3.3. Events

If any event described below occurs, the information below must be reported.

Refer to 23. *Procedures for Adverse Events* and 24. *Evaluation of Adverse Events* for information that must be reported in case of serious adverse events.

If a subject is transported to another medical institution due to an event, the following information will be obtained through cooperation from the subject or family, etc., then entered into medical records and used as reference materials.

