## 7. Adverse Events

### 7.1. Definition

#### 7.1.1. Adverse events

Adverse events are any medically undesirable event observed in a subject who has received a study drug, even if the causal relationship is not known.

In other words, adverse events are any undesirable or unintended sign (including abnormal laboratory values),

symptom, or illness observed under treatment with a study drug, regardless of causal relationship with the treatment.

Aggravation of any symptom, sign, or disease preexisting granting of consent or start of observation, will be handled as a new adverse event.

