### **7.1.2. Serious adverse events**

Serious adverse events are adverse events for which any of the following apply:

1) Fatal

2) Life-threatening

The term "life-threatening" refers to an event in which the subject was at risk of death at the time of the adverse event; it does not refer to an event which hypothetically might have caused death if it were more severe.

3) Requires hospitalization or prolongation of existing hospitalization for treatment

4) Results in persistent or significant disability/incapacity

5) Is a congenital anomaly/birth defect

6) Other conditions, i.e., a medically important event for which treatment is required to avoid risks or items 1)–5) above, even if the event is not immediately life-threatening, or resulting in death or hospitalization. Examples include bronchospasm requiring intensive care in emergency rooms etc.; blood disorder or convulsions not leading to hospitalization; and drug dependence or abuse.

Explanation of "hospitalization for treatment" for serious adverse events

"Hospitalization for treatment" is defined as hospitalization of a subject in a medical institution (usually for at least one night) for treatment of adverse events, even if no particular treatment is performed (resting cure). This does not include hospitalization for examination or treatment of the primary disease or complications not aggravated from pre-observation conditions; hospitalization for convenience or personal reasons not intended to treat adverse events; and hospitalization for treatment or examination that was already scheduled prior to the first visit.

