### **23.2. Serious adverse event reporting**

#### **23.2.1. Serious adverse events (SAE) requiring immediate reporting**

The following SAEs require immediate reporting:

- 1) All SAEs occurring during the observation period, regardless of their relationship with the study drug.
- 2) SAEs for which causal relationship with study drugs cannot be denied occurring during the course of a follow-up investigation of an adverse event (see 25. *Follow-Up Investigation of Adverse Events*), or an SAE which becomes serious during a follow-up investigation and for which causal relationship with study drugs cannot be denied.
- 3) SAEs occurring after completion of the study period reported to the investigator/subinvestigator by the subject, and for which the causal relationship to the study drugs cannot be denied according to the investigator/subinvestigator.

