#### 24.4. Seriousness

Seriousness of adverse events is classified into 2 levels as follows in accordance with 7.1.2. *Serious adverse events*.

1. Serious
2. Not serious

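### Recurrent strokes rated serious enter the any-SAE comparison, and no stroke-excluded SAE contrast that allows for time at risk is planned (minor)

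*Supplement*

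**What the plan says.** SAP 10.3 defines SAEs as adverse events rated serious, which "will be considered serious adverse events and analyzed in the same manner as indicated in subsections 1) and 2) of section 10.1". Subsection 1) of SAP 10.1 gives "The number of patients with adverse events and their incidence (100 x no. of patients with adverse events / no. of ITT patients") by group with a chi-square test. Subsection 2) repeats this by system organ class and preferred term. Only events within the observation period count.

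Protocol v1.3 decides what can enter that row:

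- Section 7.1.1: "Adverse events are any medically undesirable event observed in a subject who has received a study drug, even if the causal relationship is not known". Efficacy endpoints are not set aside.
- Section 7.1.2: an event is serious if, among other criteria, it is fatal, disabling or leads to hospitalisation for treatment. The nearest thing to an exemption removes "hospitalization for examination or treatment of the primary disease or complications not aggravated from pre-observation conditions".
- Section 6.3.3 (evaluated events, including ischaemic stroke) refers the investigator to the adverse event sections "for information that must be reported in case of serious adverse events".
- Section 23.2.1 requires immediate reporting of "All SAEs occurring during the observation period, regardless of their relationship with the study drug".
- Section 24.4: "Seriousness of adverse events is classified into 2 levels as follows in accordance with" section 7.1.2.
- Section 5.3: observation stops at any 6.3.3 event and when study drug is discontinued.

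The other safety summaries with a between-group test are adverse drug reactions, serious adverse drug reactions (SAP 10.4) and haemorrhagic events (SAP 10.5). All-cause death is a secondary endpoint (SAP 9.2.4).

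**The concern.** A recurrent ischaemic stroke will usually be both the primary efficacy event and an SAE. If cilostazol prevents strokes as assumed, the any-SAE share falls on DAPT for that reason alone. The fall is real, but a level or lower total can then coexist with more serious harm of other kinds, and readers commonly take an SAE total as the summary of tolerability. Harm confined to one organ class, bleeding and deaths would still be visible. What the planned tables lack is an overall contrast for non-stroke serious harm spread thinly over several classes.

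The row is also a simple proportion of ITT patients. Observation ends at drug discontinuation and at any evaluated event, so the arms may be watched for different lengths of time, and a proportion does not correct for that.

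**Working it through.** **Plan's own figure.** Hazard ratio 0.70, two-sided 5%, 80% power: 4(1.960+0.842)²/(ln 0.70)² = 247 events. With hazards 0.04 and 0.028, uniform accrual over 2.5 years and 1 to 3.5 years of follow-up, event probabilities are 0.0857 and 0.0609. 247/(0.0857+0.0609) gives about 1,686 per group, against 1,688 stated. The stroke rates can be carried forward.

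**Inputs.** From the documents: stroke 4% and 2.8% per year (SAP 4), mean observation about 2 years (protocol 11.4.1), 2,000 per arm. Assumed, because the documents do not give them: risk b of other SAEs on SAPT over 2 years (5, 10, 15, 30%) and the fraction f of strokes rated serious (1 or 0.5), with strokes and other SAEs independent.

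**Stroke contribution.** 1−0.96² = 7.84% and 1−0.972² = 5.52%. The difference of 2.32 points × 2,000 is about 46 fewer DAPT patients. Staggered entry with 5% per year dropout gives about 161 v 115, a difference of 47.

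**Offset.** Any-SAE risk = 1−(1−b)(1−f·IS), where IS is the arm's stroke risk. The DAPT other-SAE risk x that makes the totals equal solves (1−x)(1−f·0.0552) = (1−b)(1−f·0.0784). Hazard ratio = ln(1−x)/ln(1−b). Power is for x v b in a stroke-excluded two-proportion test at two-sided 5%.

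| f | b | any-SAE, SAPT v DAPT, if other SAEs equal | fewer on DAPT | x | extra DAPT patients offset | HR | power |
|---|---|---|---|---|---|---|---|
| 1 | 5% | 12.45 v 10.25% | 44 | 7.33% | 47 | 1.48 | 87% |
| 1 | 10% | 17.06 v 14.97% | 42 | 12.21% | 44 | 1.24 | 60% |
| 1 | 15% | 21.66 v 19.69% | 39 | 17.09% | 42 | 1.15 | 44% |
| 1 | 30% | 35.49 v 33.87% | 32 | 31.72% | 34 | 1.07 | 22% |
| 0.5 | 5% | 8.72 v 7.62% | 22 | 6.13% | 23 | 1.23 | 35% |
| 0.5 | 10% | 13.53 v 12.48% | 21 | 11.07% | 21 | 1.11 | 20% |
| 0.5 | 15% | 18.33 v 17.35% | 20 | 16.01% | 20 | 1.07 | 14% |
| 0.5 | 30% | 32.74 v 31.93% | 16 | 30.83% | 17 | 1.03 | 8% |

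A clearer excess shows the contrast between the two rows. At b = 10%, a true risk ratio of 1.3 for other SAEs and all strokes serious, the stroke-excluded total has about 84% power and the planned any-SAE total about 9%.

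**Can a reader recover the non-stroke total?** Because an evaluated event ends observation, a patient contributes essentially one stroke. Subtracting stroke patients from the any-SAE total loses only those who had another SAE before the stroke. With constant hazards, equal other-SAE hazards and all strokes serious, that overlap is 3.9 / 7.9 / 11.9 / 24.6 SAPT and 2.8 / 5.6 / 8.4 / 17.4 DAPT patients at b = 5 / 10 / 15 / 30%. The group difference is therefore misstated by about 1.1 / 2.3 / 3.5 / 7.2 patients.

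**Time at risk.** Let ho = −ln(1−b)/2, hs the stroke hazard, hc the discontinuation hazard. Other-SAE risk seen = ho/(ho+hs+hc)·[1−exp(−2(ho+hs+hc))]. With equal true ho in both arms, DAPT minus SAPT patients per 2,000:

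| discontinuation per year, SAPT v DAPT (assumed) | b = 5% | 10% | 15% | 30% |
|---|---|---|---|---|
| none | +1.2 | +2.3 | +3.5 | +6.7 |
| 5% v 5% | +1.1 | +2.2 | +3.2 | +6.3 |
| 5% v 10% | −3.6 | −7.1 | −10.5 | −20.3 |
| 5% v 15% | −8.1 | −16.2 | −24.0 | −46.6 |

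The first-SAE rate stays at ho in both arms (2.56 / 5.27 / 8.13 / 17.83 per 100 person-years) if stopping is unrelated to SAE risk. A stroke-excluded proportion alone would not be enough.

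**The case against.** The case against acting has four parts.

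1. A reader might infer that non-stroke serious harm would be hidden beyond recovery, since one patient can sit in several preferred-term rows. The documents do not support that: the 5.3 stopping rule limits the overlap, and subtraction lands within about 1-7 patients of the true group difference. This part stands. What remains is that the contrast is not planned and has no confidence interval.
2. Serious adverse drug reactions (SAP 10.4) already give a patient-level total, and protocol 24.5 lets an event be rated unrelated when it may be due to the primary disease, so most recurrences may drop out. This stands in part. The total depends on causality ratings by investigators who learn the allocation from the enrolment system (4.1), with no placebo described. An all-cause count does not depend on those ratings.
3. Whether strokes reach the SAE data is a reading of definitions. Section 6.3.2 lists events separately from "Presence or absence of adverse events or serious adverse events", and the CRF manual is not shown. This is a real limit. But no text exempts endpoints, and the 7.1.2 carve-out covers only disease that has not worsened, which a new stroke is not.
4. The added comparison is weak: power is 60% or less in seven of the eight scenarios tabulated, and the rate is unbiased only if stopping is unrelated to SAE risk, whereas 5.3 also allows withdrawal for serious adverse events. Both limits stand. The gain is mainly a visible estimate.

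**Conclusion.** The point holds as a minor improvement to the safety report. On the protocol's definitions, strokes rated serious enter the any-SAE row, and an equal total could offset about 17-47 extra DAPT patients with other SAEs per 2,000. That range rests on the plan's stroke rates, two years of observation, independence, and two inputs that the documents do not give: the background SAE risk and the share of strokes rated serious. TIA is left out because the plan gives no rate.

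A reader might go further and infer that the any-SAE comparison is wrong or that the plan would conceal harm. Neither follows. The row counts all SAEs correctly, no stopping rule or primary conclusion rests on it, and organ-class rows, bleeding, deaths and the IDMC's listings remain informative.

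**What to change.** In SAP 10.3, keep the all-SAE row. Beside it, report by group:

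- the number and proportion of patients with any SAE other than ischaemic stroke or TIA recorded as evaluated events;
- the rate of first such SAE per person-year;
- the between-group difference in each, with a 95% CI.

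Keep haemorrhage, myocardial infarction and other vascular events in. Heart failure and uncontrolled angina are excluded at entry on safety grounds (protocol 3.3), so cardiac events may be harm. State that the comparison is descriptive with low power in most scenarios, and that the rate is unbiased only if stopping is unrelated to SAE risk. One sentence should also say whether evaluated events are entered as SAEs.

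The cost is SAP wording, one filter, one person-year denominator and one more table. Event dates (protocol 24.2) and observation dates (SAP 6.2.4) are already collected. The interim review (protocol 11.4.2) needs no change.
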